## 3.5 Study Participants:

Participants will be residents within the identified catchments areas at each of the study sites as described above. Eligible subjects will be:

1. current residents who have resided in their respective communities for at least 6 months prior to enrollment into the study,
2. aged 30 – 75 years,
3. currently not known to be pregnant
4. have no plans of migrating out of the study area over the next 12 months from the date of enrollment into the study,
5. able to provide written informed consent,
6. agree to allow home visits and follow-up contacts as part of participating in the trial,
7. no previous diagnosis with diabetes, or diagnosis of diabetes of no longer than 12 months prior to being screened for enrollment into the study
8. have a positive confirmatory test of pre-diabetes or diabetes

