***Recruitment:***

Once the sensitization activities are completed, trained Field Research Assistants (FRA) will approach households within each of the specified cluster communities, explaining the study to household members, and seeking consent to participate in screening for the trial. The FRA will seek a written pre-eligibility screening informed consent from adult members of the household. The FRA will then administer a short screening form to consenting adults to identify potential trial participants. In this first stage of screening, potential eligible household members would need to meet the following criterion:

1. current resident that have resided in their respective communities for at least 6 months prior to the date of screening
2. have no plans of migrating out of the study area over the next 12 months from the date of enrollment into the study,
3. aged 30 – 75 years,
4. currently not known to be pregnant
5. no previous diagnosis with diabetes, or diagnosis of diabetes of no longer than 12 months prior to the date of screening

The FRA will arrange an appointment with household members that meet the preceding criteria to return early morning on an agreed date, for a fasting plasma glucose (FPG) test. The FRA will return to the household on the agreed morning and conduct the FPG test usig an AccuCheck glucometer.

The FRA will arrange for a second FPG test for subjects with the first (Test 1) FPG results of at least 6.1 mmol/L (see Figure 3.7). Potentially eligible household members will those with a second (Test 2) FPG test result of at least 6.1 mmol/L, and will be referred to the respective cluster health facility for a confirmatory eligibility FPG test. The subjects will be given a referral note, and advised to report to the health facility within seven days, after an overnight fast on the day they report, with no exercise or smoking.

On presentation to their respective health facility with the referral note, a third FPG test will be conducted to confirm eligibility. Subjects will be classified as: a) normal if two of their FPG tests are less than 6.1 mmol/L, b) pre-diabetes if two of their FPG tests is between 6.1 and 6.9 mmol/L, and, c) diabetic if two of their FPG test results are greater than 6.9 mmol/L. Figure 12 and Table 12 summarizes the decision guide to identify eligible subjects in Uganda, as far as their FPG levels are concerned.

Figure 12: Algorithm for sequence of screening tests for Uganda

[figure not shown]

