**3.6.2.** **Facility recruitment**

Recruitment will take place at the two selected facilities. Persons presenting at the facilities who are either diagnosed with T2DM, or present with NCDs risk factors, including obesity, high blood pressure and/or impaired glucose tolerance, will be invited to participate in the trial. They will be recruited when visiting the facility for routine clinical care or upon referral from the community as per the above outlined protocol. Subjects will be classified as diabetic if two consecutive FPG tests > 6.9 mmol/L and as pre-diabetic if two consecutive FPG tests are between 6.1-6.9 mmol/L. A third FPG test may be needed to validate different test results (Figure 13 and Table 13).

Following eligibility confirmation, an ‘Eligibility Confirmation Form’ will be administered and written informed consent sought from the subject prior to study enrollment. Briefly, the study manager at the health facility will provide information on SMART2D study objectives, procedures, benefits and risks of participating, as well as confidentiality issues. Participants will receive a consent form and continue to receive standard medical care as needed, and as available at the health facility. Administration of any study procedures will only happen after eligible subjects have consented to participate in the study, upon which they will be enrolled and given a unique study number.

*Figure 13 Algorithm for sequence of screening tests for South Africa*

[figure not shown]

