### 3.6.3 Sweden

In Sweden, since the suburbs chosen varied in terms of the composition of immigrant groups and the overall socio-economic status, the catchment area of each of the participating health centres were divided into zones using postal codes. These zones were randomly allocated to primary care versus integrated care, taking care to prevent contamination and spillover. Participants are recruited to the trial through community screening. The research team with input from health centres and municipalities have identified opportunities and spaces in the community to carry out screening activities. Both research staff as well as outreach workers from the municipalities are involved in mobilizing community members and inviting them to participate in the screening, by: 1) facilitating access to the target population through local NGOs, immigrant associations, religious bodies, such as churches and mosques, and cafes or other ventures owned by immigrant groups; 2) identifying and facilitating access to spaces to set up the screening activities such as shopping malls, local library, municipality hall or other public spaces such as swimming halls.

Community screening activities are carried out by the research team on weekdays and weekends using a combination of FINDRISC [J. Lindström et al. 2003], and hemoglobin A1c (HbA1c) test (both point-of-care and lab-based) using a recruitment algorithm summarized in Figure 14 and Table 14. All individuals with HbA1c values in the diabetes or pre-diabetes range are referred to the health centres to be registered and enrolled into the primary care only arm, or the integrated care arm as the case may be.

Figure 14: Algorithm for sequence of screening tests for Sweden

[figure not shown]

Table 14: Decision guide to enroll for Sweden

| **Test 1 (POC HbA1c)*** | **Test 2 (Lab HbA1c)*** | **Outcome** |
| --- | --- | --- |
| HbA1c = 42-47 | HbA1c = 42-47 | **Pre-D: RECRUIT** |
|  | HbA1c ≥ 48 | **T2D: RECRUIT** |
|  | HbA1c < 42 | NOT ELIGIBLE |
| HbA1c ≥ 48 | HbA1c ≥ 48 | **T2D: RECRUIT** |
|  | HbA1c = 42-47 | **Pre-D: RECRUIT** |

*HbA1c values based on WHO and ADA recommendation[WHO 2011; ADA 2016]

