## 3.9 Outcomes of interest:

*Primary outcomes of interest*

Among participants with pre-diabetes, the primary outcome of interest will be reduction in plasma glucose between baseline and month 12 of follow-up. We hypothesize that participants with pre-diabetes in the facility + community arm will on average have a higher reduction in their HbA1c reading by the end of follow-up compared to participants with pre-diabetes in the facility alone arm, and the current practice arm in Uganda.

Regarding participants with type 2 diabetes, research has shown that, reduction of HbA1c level by 1% among such individuals leads to: a) 19% less likelihood of cataracts, b) 16% less likelihood of heart failure, and c) 43% less likelihood of amputations or death due to peripheral vascular disease [Anon 1993]. Further the UK Prospective Diabetes Study (UKPDS) [King et al 1999], and the Diabetes Control and Complications Trial (DCCT) demonstrated that improving HbA1c by 1% for people with type 1 diabetes *or* type 2 diabetes cuts the risk of microvascular complications by 25%. Therefore among participants with diabetes, the primary outcome of interest will also be reduction of their plasma glucoce levels. A participant will be classified as having had their plasma glucose reduced if:

1. Their HbA1c reading at month 12 is reduced to below 53 mmol/mol, or
2. Their HbA1c reading at month 12 is 5 mmol/mol below their baseline reading.

*Secondary outcomes of interest*

Secondary outcomes in this trial will include:

a) Incidence of diabetes among participants with pre-diabetes

b) Incidence of conversion from a state of pre-diabetes to normal plasma glucose levels.

c) Incidence of adverse events, including hospitalizations due to hypo- or hyperglycemia, or complications of diabetes.

d) Behavioral outcomes, including diet, physical activity, foot care, tobacco and alcohol consumption.

e) Costs of implementation of the intervention elements

f) Participant satisfaction with the individual intervention elements, including self-management

g) Differences between the country sites, in regard to baseline context infrastructure for prevention and management of T2D

h) Degree of implementation of intervention elements in each country, and differences between country sites informed by site-specific process evaluations

i) Effect of the interventions on perceptions towards diabetes, life style measures including physical activity, dietary behavior, etc.

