Thus we will aim at maximizing the proportion of participants with diabetes whose blood sugar levels has been reduced, per the criteria defined above. We aim at being able to detect a difference of at least 2% in the percentage of participants with diabetes with reduced plasma glucose levels by month 12 between the trial arms (effect size). The required sample size before adjusting for clustering, at 80% power and 5% level of significance is 58 participants per arm. We have also assumed that in the intervention arm we shall attain reduction in plasma glucose per the criteria given above, in 30% of participants with diabetes (P_1_= 0.3). For this first stage calculations, we used the formula as described in Hayes and Bennett (1999) [Hayes 1999] for proportions, that is:

[figure not shown]

where: $n_{i}$ = initial sample size (58)

$P_{0}$ = Proportion of participants with diabetes in the comparison (control) arm, whose plasma glucose levels are controlled by month 12 (32%)

$P_{1}$ = Proportion of participants with diabetes in an intervention arm, whose plasma glucose levels are controlled by month 12 (30%)

For an estimate of inter-cluster correlation (ICC) among individuals with diabetes, we found only two publications of cluster randomized trials reporting ICC estimates among diabetes patients, one by Littenberg et al (2006) in which they report an inter-cluster correlation (ICC) coefficient for HbA1c among patients with diabetes of 0.055 [Littenberg et al. 2006]; and another by Singh et al (2015) in which they report an ICC coefficient of 0.091 [Singh et al. 2015]. We use some of these estimates. For Uganda we used an ICC value of 0.0.091 to obtain a sample size of 128 participants, for South Africa we used an ICC value of 0.020 to obtain a sample size of 136, whereas for Sweden we also used an ICC value of 0.020 to obtain a sample size of 81; all per study arm.

Once again for Sweden, there will be a further interest to compare the primary outcome of interest between immigrant participants of non-European origin versus immigrant participants of European origin. In order to allow for this sub-analysis, the sample size of 81 for Sweden was doubled to 162 to enable detection of the same effect size immigrant participants of non-European origin versus immigrant participants of European origin.

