## 3.13 Statistical analysis Plan

### 3.13.1 Primary intervention efficacy analysis:

We will use intention-to-treat analyses for all primary outcomes, that is, all participants will be analyzed as assigned to their respective study arms. Since the unit of analysis for the primary outcome of interest are the individual participants, to minimize the effect of within cluster correlations, we will employ generalized estimating equations (GEEs) to evaluate changes over time in HbA1c values as a continuous variable among participants with pre-diabetes; and the proportion of participants with stabilized plasma glucose among participants with diabetes, in relation to assigned trial arm. Thus we use multivariable linear regression mixed effects modeling with a random intercept, unstructured correlation matrix and robust standard errors, to evaluate changes over time in HbA1c, and logistic regression analysis to compare the proportion of participants with stabilized plasma glucose among participants with diabetes.

Missing data are expected due to missed appointments, drop-outs, loss-to-follow-up and/or death. One technique to deal with missing data when the outcome is continuous, is hierarchical linear modeling (HLM; also called random effects regression) [Singer et al. 2003].

We do not anticipate differences in the intercept within each site, as randomization is expected to balance out baseline differences between the groups. However, there may be differences in the intercepts between sites, reflecting differences within the client populations in each site. We anticipate that the primary factor affecting the slope (i.e., the rate of change of the outcome measure) will be group membership (i.e, facility only or facility plus community intervention). If there is any significant unexplained variance after baseline differences and site membership have been accounted for, we can look for other factors influencing the slope, such as sex, age, co-morbidities, etc. Another analytic option that will be considered is generalized estimating equations (GEE) [Zeger et al. 1986], which can adjust for clustered, serially correlated data with missing values. The choice of techniques will be based on the nature of the data.

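### The diabetes responder rule puts no baseline condition on its below-53 mmol/mol criterion, although participants can enter already below 53

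*Protocol*

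**What the plan says.** Protocol 3.9 gives the primary outcome in participants with diabetes as reduction of plasma glucose. It classifies a participant as reduced on either of two criteria:

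- Criterion 1: "Their HbA1c reading at month 12 is reduced to below 53 mmol/mol".
- Criterion 2: "Their HbA1c reading at month 12 is 5 mmol/mol below their baseline reading".

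The criteria are joined by *or*, and Section 3.10 repeats them. Neither section states a baseline HbA1c that a participant must have for criterion 1 to apply.

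Entry as diabetes differs by country:

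- Sweden (3.6.3, Table 14) uses HbA1c: "HbA1c ≥ 48 | HbA1c ≥ 48 | T2D: RECRUIT".
- Uganda (3.6.1, Recruitment) uses fasting glucose: "diabetic if two of their FPG test results are greater than 6.9 mmol/L".
- South Africa (3.6.2, Facility recruitment) does likewise: "Subjects will be classified as diabetic if two consecutive FPG tests > 6.9 mmol/L".

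Section 3.5 also admits people with a "diagnosis of diabetes of no longer than 12 months prior to being screened for enrollment into the study". The baseline questionnaire (Section 4, medical and medication history) asks about current insulin and oral agents, so some may already be treated.

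For the analysis, Section 3.13.1 plans "logistic regression analysis to compare the proportion of participants with stabilized plasma glucose among participants with diabetes". Section 3.10 describes the same outcome as controlled blood sugar.

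**The concern.** The outcome is named as a reduction, but criterion 1 looks only at where the participant ends. Anyone who starts below 53 mmol/mol is at or close to success on the first day, in either arm. Because the criteria are joined by *or*, the 5 mmol/mol requirement does not correct this.

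The wording also leaves the classification of these people open. The word *reduced* in criterion 1 suggests that some fall is needed. The words *controlled* (3.10) and *stabilized* (3.13.1) suggest a plain threshold. Different readings give different responder counts for a primary endpoint.

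Three things are at stake:

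- If people starting below 53 succeed at much the same rate in both arms, they dilute the arm difference.
- Sites are to be pooled, yet one has an entry floor of 48 and two have no HbA1c floor, so the rule behaves differently by country.
- With 9, 4 and 2 clusters in Uganda, Sweden and South Africa, a chance imbalance in the share starting below 53 feeds straight into the responder rates.

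**Working it through.** **Step 1. The readings side by side.** HbA1c in mmol/mol, baseline to month 12. Criterion 2 is taken as a fall of at least 5 and is available under every reading.

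| Path | Criterion 1 as plain threshold | Criterion 1 needs some fall | Criterion 1 needs baseline of 53 or more |
| --- | --- | --- | --- |
| 48 to 52 | success | failure | failure |
| 50 to 50 | success | failure | failure |
| 52 to 51 | success | success | failure |
| 52 to 47 | success | success | success |
| 54 to 52 | success | success | success |
| 70 to 66 | failure | failure | failure |

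Only the last reading never counts a person starting below 53 without a fall of 5. The protocol does not choose among the three.

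**Step 2. The plan's own figure.** Section 3.10 states that the number needed "at 80% power and 5% level of significance is 58 participants per arm", for a 2-point difference. The unpooled formula is n = (1.96 + 0.8416)² × [P0(1 − P0) + P1(1 − P1)] / (P0 − P1)².

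- 30% vs 32%: 7.849 × (0.21 + 0.2176) / 0.0004 ≈ 8,390 per arm. The 58 does not follow.
- 30% vs 55%: 7.849 × (0.21 + 0.2475) / 0.0625 ≈ 57.5.
- 30% vs 10%: 7.849 × (0.21 + 0.09) / 0.04 ≈ 58.9.

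The mismatch is a separate sample-size problem. It matters here because the protocol supplies no usable pair of responder rates. The pair 30% and 55% is used below only because it gives roughly the stated 58; the 55% is an assumption and appears nowhere in the protocol.

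**Step 3. Dilution.** Let a share f start below 53 and succeed with the same probability s in both arms, and let the rest succeed with probabilities p0 and p1. The arm rates are f·s + (1 − f)·p0 and f·s + (1 − f)·p1, so the difference is (1 − f)(p1 − p0), whatever s is. With p0 = 30%, p1 = 55% and s = 1, all assumed:

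| f (assumed) | Control | Intervention | Difference | Power at 58 per arm, before clustering |
| --- | --- | --- | --- | --- |
| 0% | 30% | 55% | 25 points | 80% |
| 20% | 44% | 64% | 20 points | 60% |
| 30% | 51% | 68.5% | 17.5 points | 50% |
| 40% | 58% | 73% | 15 points | 41% |

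The power column uses the unpooled normal approximation. For f = 20%, the standard error is √[(0.44 × 0.56 + 0.64 × 0.36)/58] = 0.0907, and 0.20/0.0907 − 1.96 = 0.25, which gives 60%. This is not the trial's power: 58 is the figure before the clustering and follow-up adjustments.

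**Step 4. Relaxing the equal-success assumption.** Both criteria were simulated with assumed normal baselines (mean 55 to 75, SD 8 to 20 mmol/mol).

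- The share below 53 was 5% to 26% with a floor of 48, and 13% to 40% without an HbA1c floor.
- If nobody changes at all, exactly that share are responders under the threshold reading. None are if criterion 1 needs a baseline of 53 or more.
- With a true 5 mmol/mol arm effect and an assumed SD of individual change of 3 to 8, the arm difference was 20 to 45 points under the threshold reading, against 23 to 48 points with the baseline condition. Setting by setting, the loss was 0 to 14 points. It was largest when many start below 53 and individual change is small.

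**The case against.** The strongest reply is textual. Section 3.9 speaks of reduction throughout, so a person who stays at 50 or rises from 48 to 52 has not been reduced and would not count. That is a fair reading, and a reader should not infer that the rule certainly passes people who do not change. It does not settle the matter: the other labels point to a threshold, and on the literal reading a fall from 52 to 51 still succeeds.

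A second reply is that keeping someone at 49 for a year is good control and may deserve to count. This stands as a design choice. The protocol would then have to say so and stop calling the outcome a reduction.

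Four stronger inferences are tempting and are not supported:

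- *Many participants start below 53.* The protocol gives no baseline HbA1c distribution.
- *Automatic successes push the control rate above the planned 30%.* Section 3.10 applies its 30% to the whole rule in all participants with diabetes, so it already includes anyone starting below 53. The text there assigns 30% to the intervention arm and 32% to control; only Table 16(b) assigns 30% to control.
- *The arm difference must shrink.* If controls starting below 53 drift above it and intervention participants do not, that group adds to the difference.
- *The responder model omits baseline HbA1c.* Section 3.13.1 names logistic regression without listing covariates, and these may properly be set in a statistical analysis plan.

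**Conclusion.** The defect lies in the definition and needs no assumed figure. Criterion 1 has no baseline condition, entry admits people already below 53 at all three sites, and the *or* prevents criterion 2 from correcting this. The protocol also leaves open which of three readings applies.

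Its size cannot be fixed from the documents. Under equal success in both arms the difference is multiplied by 1 − f. With the assumed 30% vs 55% and f of 20% to 40%, it falls from 25 points to between 20 and 15. When people starting below 53 are allowed to change, the simulated loss is 0 to 14 points. Dilution is therefore the expected direction but not a certainty, and the power figures above illustrate the mechanism only.

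The point merits a change before analysis because it concerns a primary endpoint and is cheap to resolve.

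**What to change.** 1. In 3.9 and 3.10, apply criterion 1 only to participants with baseline HbA1c of 53 mmol/mol or more, and classify the others by criterion 2, worded as a fall of at least 5 mmol/mol. If maintained control is meant to count as success, say so instead and rename the outcome.
2. Adjust the responder model for baseline HbA1c, and report results separately for baseline below 53 and for 53 or more.
3. Add a supportive analysis of month-12 HbA1c as a continuous outcome adjusted for baseline in participants with diabetes. This would be new: for pre-diabetes, 3.13.1 describes changes over time and does not specify a baseline-adjusted month-12 analysis.
4. Restate the expected responder proportions so that they match the rule adopted, with the assumed share starting below 53 made explicit.

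Table 15 already schedules HbA1c at baseline and month 12 at all sites, so no new data are needed. The cost is wording, one covariate and restated planning proportions. The drawback of the first option is that people kept below 53 without a 5 mmol/mol fall count as non-responders; the report by baseline group would show how many there are.

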## 3.10 Sample size Determination

Although the overall aim during data analysis will be to combine participants across all the three country sites, it is recognized that: a) there will most likely be baseline differences across the country sites reflecting the different population characteristics between the countries; and, b) each site will want to analyze data from their site-specific arms. Thus the sample was calculated such that differences between the trials arms in regard to primary outcomes can be detected at each study site separately when desired.

The sample size for this trial has been determined based on the primary hypothesis that by the end of follow-up, the “facility plus community” arm will be superior to the “facility alone” arm, and the current practice arm in Uganda, with respect to: a) mean HbA1c readings among participants with pre-diabetes, and b) the proportion of participants with diabetes with controlled blood sugar levels.

*Sample size for participants with pre-diabetes*

With the aim of being able to detect an average difference between any two trial arms, in mean HbA1c by month 12 of at least 3 mmol/mol (effect size), with a standard deviation of 2.5 mmol/mol in the intervention arm, and a standard deviation of 2.5 mmol/mol in the comparison (control) arm; the required sample size before adjusting for clustering, at an 80% power and 5% level of significance is 34 participants per arm. For this first stage calculations, we used the formula as described in Hayes and Bennett (1999) [Hayes et al. 1999] for a continuous outcome:

$$Initial sample size(n_{i})=\left[ \frac{\left( Z_{\alpha/2}+Z_{\beta} \right)^{2}*\left( \sigma_{0}^{2}+\sigma_{1}^{2} \right)}{\left( \mu_{0}-\mu_{1} \right)^{2}} \right]$$

where: $Z_{\alpha/2}$ = standard normal distribution value at $\alpha$ level of significance

= standard normal distribution value at level of significance

[figure not shown]

[figure not shown]

[figure not shown]

[figure not shown]

$\alpha$ = level of significance

= type 2 error, for which (1-$\beta$) is the power of the study to detect the desired effect size

[figure not shown]

[figure not shown]

$\sigma_{0}^{2}$ = variance of outcome variable (HbA1c) at month 12 in the comparison (control) arm

$\sigma_{1}^{2}$ = variance of outcome variable (HbA1c) at month 12 in the intervention arm

$\mu_{1}$ = mean value of outcome variable (HbA1c) at month 12 in the intervention arm

$\mu_{0}$ = mean value of outcome variable (HbA1c) at month 12 in the comparison (control) arm

$\left( \mu_{0}-\mu_{1} \right)$ = minimum effect size to be detected

[figure not shown]

[figure not shown]

The necessary sample size for a cluster randomized trial depends on the variation in the intervention effects between the arms, and the clustering due to trial arm allocation (which reduces the variance of the difference between the arms), and the correlation between the repeated observations in each participant. Given that we have a fixed number of health facilities (clusters), to adjust for clustering we used a formula for fixed number of clusters and fixed number of participants within clusters as described in Hemming et al (2011) page 19 [Hemming et al. 2011].

$$Sample size per cluster=\frac{n_{i}*k*\left( 1-\rho\right)}{\left( k-n_{i}*\rho\right)}$$

where: $n_{i}$ = initial sample size

$k$ = number of clusters

= inter-cluster correlation

[figure not shown]

[figure not shown]

It is important to note that each site will be using different numbers of clusters; specifically Uganda will be working in 9 clusters, Sweden in 4 clusters, whereas South Africa will be working in 2 clusters. Thus different inter-cluster correlation (ICC) coefficient values are expected. We were unable to find published literature providing estimates for ICC coefficients for HbA1c among persons with pre-diabetes. We therefore explored various values of ICC coefficients for each site, and used values that provided the highest sample sizes to detect the desired effect size. For Uganda we used an ICC value of 0.200 to obtain a sample size of 112 participants, for South Africa we used an ICC value of 0.044 to obtain a sample size of 129, whereas for Sweden we used an ICC value of 0.06 to obtain a sample size of 79; all per study arm. For Sweden, there will be a further interest to compare the primary outcome of interest between immigrant participants of non-European origin versus immigrant participants of European origin. In order to allow for this sub-analysis, the sample size of 79 for Sweden was doubled to 158 to enable detection of the same effect size between immigrant participants of non-European origin versus immigrant participants of European origin.

Further, we project a loss to follow-up of up to 10% over the 12 months follow up, thus the sample sizes obtained were accordingly adjusted upwards by 10%. Table 16 (a) provides a summary of the estimates used, and the sample size estimates obtained.

Table 16 (a): Parameter value estimates used in sample size calculations for participants with pre-diabetes

| **Parameter** | **Estimate** | | |
| --- | --- | --- | --- |
| Level of significance (α) | 5% | | |
| Power (1-β) | 80% | | |
| Primary outcome of interest | Mean change in HbA1c reading | | |
| Standard deviation (σ), of mean change in HbA1c | 2.5 | | |
| Minimum anticipated difference between arms, in primary outcome by month 12 | $\left( \mu_{0}-\mu_{1} \right)$ =  5 mmol/mol | | |
| Required sample size per arm, before adjusting for clustering (*n_i_*) | 34 | | |
|  | Uganda | South Africa | Sweden |
| Number of clusters | 9 | 2 | 4 |
| Inter-cluster correlation (ρ) | 0.200 | 0.044 | 0.070 |
| Sample size per arm, after adjusting for clustering (n) | 112 | 129 | 158 |
| Sample size per arm, after further adjusting for estimated loss to follow-up of 10% | 124 | 142 | 174* |

* *For Sweden, at least 87 participants with pre-diabetes will need to be immigrants of non-European origin, and at least 87 participants with pre-diabetes will need to be immigrants of European origin*

*Sample size for participants with diabetes*

A prospective cohort study among patients with diabetes in the United Kingdom showed that people with type 2 diabetes who reduce their HbA1c level by 1% are: a) 19% less likely to suffer cataracts, b) 16% less likely to suffer heart failure, and c) 43% less likely to suffer amputation or death due to peripheral vascular disease [Stratton et al. 2000]. Therefore among participants with diabetes, we aim at reducing their plasma glucose levels by month 12. A participant with diabetes will be defined as having had their plasma glucose reduced if:

1. Their HbA1c reading at month 12 is reduce to below 53 mmol/mol, or
2. Their HbA1c reading at month 12 is 5 mmol/mol below their baseline reading.

Thus we will aim at maximizing the proportion of participants with diabetes whose blood sugar levels has been reduced, per the criteria defined above. We aim at being able to detect a difference of at least 2% in the percentage of participants with diabetes with reduced plasma glucose levels by month 12 between the trial arms (effect size). The required sample size before adjusting for clustering, at 80% power and 5% level of significance is 58 participants per arm. We have also assumed that in the intervention arm we shall attain reduction in plasma glucose per the criteria given above, in 30% of participants with diabetes (P_1_= 0.3). For this first stage calculations, we used the formula as described in Hayes and Bennett (1999) [Hayes 1999] for proportions, that is:

[figure not shown]

where: $n_{i}$ = initial sample size (58)

$P_{0}$ = Proportion of participants with diabetes in the comparison (control) arm, whose plasma glucose levels are controlled by month 12 (32%)

$P_{1}$ = Proportion of participants with diabetes in an intervention arm, whose plasma glucose levels are controlled by month 12 (30%)

For an estimate of inter-cluster correlation (ICC) among individuals with diabetes, we found only two publications of cluster randomized trials reporting ICC estimates among diabetes patients, one by Littenberg et al (2006) in which they report an inter-cluster correlation (ICC) coefficient for HbA1c among patients with diabetes of 0.055 [Littenberg et al. 2006]; and another by Singh et al (2015) in which they report an ICC coefficient of 0.091 [Singh et al. 2015]. We use some of these estimates. For Uganda we used an ICC value of 0.0.091 to obtain a sample size of 128 participants, for South Africa we used an ICC value of 0.020 to obtain a sample size of 136, whereas for Sweden we also used an ICC value of 0.020 to obtain a sample size of 81; all per study arm.

Once again for Sweden, there will be a further interest to compare the primary outcome of interest between immigrant participants of non-European origin versus immigrant participants of European origin. In order to allow for this sub-analysis, the sample size of 81 for Sweden was doubled to 162 to enable detection of the same effect size immigrant participants of non-European origin versus immigrant participants of European origin.

Similarly, we project a loss to follow-up of up to 10% over the 12 months follow up, thus the sample sizes obtained were accordingly adjusted upwards by 10%. Table 16 (b) provides a summary of the estimates used, and the sample size estimates obtained.

Table 16 (b): Parameter value estimates used in sample size calculations for participants with diabetes

| **Parameter** | **Participants with Diabetics** | | |
| --- | --- | --- | --- |
| Level of significance (α) | 5% | | |
| Power (1-β) | 80% | | |
| Primary outcome of interest | % of participants with reduced plasma glucose | | |
| Proportion of participants with reduced HbA1c by month 12 in control arm ($P_{0}$) | 30% | | |
| Minimum anticipated difference between arms, in primary outcome by month 12 | $\left( P_{0}-P_{1} \right)$ = 2% | | |
| Required sample size per arm, before adjusting for clustering (*n_i_*) | 58 | | |
|  | Uganda | South Africa | Sweden |
| Number of clusters | 9 | 2 | 4 |
| Inter-cluster correlation ($\rho$) | 0.091 | 0.020 | 0.020 |
| Sample size per arm, after adjusting for clustering (n) | 128 | 136 | 81 |
| Sample size per arm, after further adjusting for estimated loss to follow-up of 10% | 141 | 150 | 90 |

* *For Sweden, at least 90 participants with diabetes will need to be immigrants of non-European origin, and at least 90 participants with diabetes will need to be immigrants of European origin*

Figure 15 summarizes the trial and the sample sizes to be used at each site per study arm.

Figure 15: Schema for the trial

^ф^265 = 124 with pre-diabetes, & 141 with diabetes

^€^292 = 142 with pre-diabetes, & 150 with diabetes

^¥^353 = 174 with pre-diabetes (87 immigrants of European origin plus 87 immigrants of non-European origin),

& 179 with diabetes (90 immigrants of European origin plus 90 immigrants of non-European origin)

Overall total participants

N=1997

Uganda

n=795

South Africa

n=584

Sweden

n=706

Follow-up

Month 3

Month 6

Month 12

Baseline evaluation

Facility only

n=292^€^

Facility+ community

n=292

Facility only

n=353^¥^

Facility+ community

n=353

Facility only

n=265^ф^

Facility+ community

n=265

Control

n=265

Randomization

